**6. Adverse events**

Adverse events will be classified according to Medical Dictionary for Regulatory Activities (MedDRA). All adverse events will be listed based on the patient code, visit time, the preferred name, the treatment group, severity, and the relationship with the study drug s. Adverse events will be summarized by number and proportion, and will be compared between the treatment groups using appropriate statistical tests(s).

**7. Analysis of laboratory and vital signs**

Assessment of laboratory classification indexes (clinical biochemistry and blood routine test) will mainly observe the proportion of patients with test results out of the range of the reference value at the last visit. Changes in laboratory and vital signs after treatment will be evaluated using the descriptive statistical analysis method.

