**2. Exclusion criteria**

2.1 Personnel of the research base who have a direct relationship with this study, as well as their close relatives. Close relatives refer to the spouse, parent, child, brother or sister, whether due to blood relationship or legal adoption.

2.2 Employees of Guangzhou Zhongyi Pharmaceutical Co., Ltd. (including staff, temporary contractual workers or designated personnel participate in this study.)

2.3 Have participated in this study in the past or other studies using sulfonylureas.

2.4 Participated in intervention medical, surgical or pharmacological research (research that gives study drugs, medical or surgical therapy) within 30 days before screening. This standard includes drugs that have not been approved by drug administration departments when entering the study.

2.5 Women of childbearing age who meet the following conditions (not yet received surgical contraception and are at the stage from menarche to 1 year after menopause):

1) Lactating women.

2) Positive pregnancy test results at the enrollment.

3) Plan to get pregnant during the research.

4) Did not take effective birth control measures within 3 months before screening.

5) Patients do not agree to continue the use of effective birth control means in the process of the trial, as determined by the investigators.

2.6 Fasting blood glucose ≥ 13 mmol/L, or HbA1c ≥ 11%.

2.7 Have more than 3 episodes of severe hypoglycemia within 6 months before the screening.

2.8 Those that who are allergic to sulfonylureas or their ingredients.

2.9 With contraindications of using metformin or sulfonylureas according to the drug package insert.

2.10 Had received treatment with exogenous insulin for more than 1 week within 3 months before screening.

2.11 Those who have a history of clinically significant heart disease within 1 year before entering the study, or with active heart diseases including myocardial infarction, severe arrhythmia, unstable angina, moderate or severe heart failure (New York Heart Society cardiac function grading: class III or IV), coronary artery bypass surgery or reconstructive vascular operation, or those who are estimated to require coronary artery bypass surgery or reconstructive vascular operation during the study.

2.12 Patients who have a history of kidney transplant or are currently receiving dialysis treatment or with serum creatinine levels reaching the upper limit of normal value.

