2.13 With obvious clinical signs or symptoms of liver disease, acute or chronic hepatitis, or alanine aminotransferase (ALT or AST) greater than 2.5 times the upper limit of normal value.

2.14 Suffering from hemoglobin disease or chronic anemia.

2.15 Suffering from active proliferative kidney disease.

2.16 Patients who are receiving any of the following medications are to be excluded:

1) Have used thiazolidinediones (TZD) within 3 months before screening.

2) Have used insulin secretagogue (sulfonylureas or nateglinide) within 1 month before screening.

3) Have used α-glucosidase inhibitors (such as miglitol or acarbose) within 1 month before screening.

4) Drugs that directly affect the gastrointestinal motility including metoclopramide and cisapride, and long-term use of macrolide antibiotics, but not limited to these drugs.

5) Systemic glucocorticoid treatment (not including local or inhaled medication) by oral administration, intravenous (IV) or intramuscular (IM) injection on a regular basis (more than 1 month) or within 1 month before screening.

2.17 Suffering from active or untreated malignancy, or malignancy in clinical remission less than 5 years (except for basal cell carcinoma or cutaneous squamous cell carcinoma, cervical carcinoma in situ, or prostate carcinoma in situ).

2.18 With a history of organ transplantation.

2.19 With a present or past history of drug or alcohol abuse that may lead to poor compliance of subjects as determined by the investigators.

2.20 For any other reason, the investigators consider it inappropriate to participate in this study.

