**1. Preliminary screening before the run-in period**

1.1 The patients sign the informed consent and accept the screening.

1.2 The history and diagnosis: history, previously extent underlying diseases, combined medications, Western medical diagnosis and TCM pattern.

1.3 Physical Examination: To measure the height, weight, waist circumference, hip circumference, and vital signs.

1.4 Laboratory indicators: blood and urine routine tests, liver and kidney function tests, fasting blood glucose, detection of HbA1c.

1.5 If all the above items meet the case selection criteria, the patient will be assigned to screening number, and enter a 4-week run-in period.

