**5. Items to be tested at the** 24th **week**

5.1 Blood and urine routine tests, liver and kidney function tests;

5.2 nocturia index (nocturia volume/24-hour urine volume);

5.3 12-lead ECG.

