**6. Items to be tested at the 48th week**

Standard postprandial 2-hour blood glucose, urinary albumin-to-creatinine ratio, blood and urine routine tests, liver and kidney function tests, 12-lead ECG, blood lipids, C-peptide, insulin, inflammatory factors (hsCRP), adiponectin; 100 cases to receive additional examination of brachial artery color Doppler ultrasonography in TCM Hospitals, patients will undergo willundergo the brachial artery color Doppler ultrasonography once again, nocturia index (nocturia volume/24-hour urine volume) will also be obtained .

Items to be measured at Central laboratory include HbA1c, C-peptide, insulin, blood lipids, C-peptide, insulin, inflammatory factors (hsCRP), adiponectin. Intravenous blood for measurement will be drown, processed according to SOP and shipped to the central laboratory.

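### The main laboratory safety measure in XII.7, out-of-range results at the last visit, omits resolved week-24 abnormalities and does not separate new from pre-existing ones

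*Protocol*

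**What the plan says.** Protocol XII.7 has two sentences. The first fixes the main measure for clinical biochemistry and blood routine: the assessment "will mainly observe the proportion of patients with test results out of the range of the reference value at the last visit". The second adds: "Changes in laboratory and vital signs after treatment will be evaluated using the descriptive statistical analysis method". It names no visit, no baseline category and no rule for what counts as new.

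The tests concerned are scheduled three times:
- at screening, week -4 (IX.1): "blood and urine routine tests, liver and kidney function tests, fasting blood glucose, detection of HbA1c";
- at week 24 (IX.5): "Blood and urine routine tests, liver and kidney function tests";
- at week 48 (IX.6): "blood and urine routine tests, liver and kidney function tests, 12-lead ECG".

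The Trial procedures table shows the same three time points. These tests are not repeated at week 0, so week -4 is the pre-treatment value.

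On liver enzymes at entry, V.2 item 2.13 excludes "alanine aminotransferase (ALT or AST) greater than 2.5 times the upper limit of normal value". Item 2.12 is stricter for creatinine and excludes patients "with serum creatinine levels reaching the upper limit of normal value".

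**The concern.** A laboratory safety summary should show who became abnormal, or became worse, on study drug. A proportion at the last visit answers a different question: who is abnormal at the end, whatever happened before. It can lose an abnormality that came and went, and it counts one that was there before the first dose.

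The protocol itself gives laboratory safety some weight. The Xiaoke Pills insert has no known adverse reactions of its own to report, and under Precautions it lists blood count abnormalities and liver damage for glibenclamide. Section I describes the earlier comparative trials as lasting 4 to 8 weeks and being of poor quality, and it names differences in adverse reactions between the two products as something this project is meant to clarify. A 48-week randomized comparison is a good opportunity to do so, and a diluted main summary uses part of it poorly.

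**Working it through.** **1. What the measure counts.** No figure in the protocol has to be reproduced, so the rule is applied to four kinds of completer, whose last visit is week 48.

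| Week -4 | Week 24 | Week 48 | Counted by XII.7? | Arose or worsened on treatment? |
|---|---|---|---|---|
| in range | out | in range | no | yes |
| in range | in range | out | yes | yes |
| mildly out | same | same | yes | no |
| mildly out | worse | worse | yes, same as the row above | yes |

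The first row is missed. The third is counted although nothing changed. The third and fourth cannot be told apart.

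**2. Who can be in the third row.** Item 2.13 leaves room for ALT or AST between 1 and 2.5 times the upper limit, provided there is no clinical liver disease or hepatitis. High creatinine (2.12) and chronic anemia (2.14) are excluded. Item 2.9 excludes insert contraindications, which include liver or kidney dysfunction and low white cells. Pre-existing abnormality is therefore chiefly mild enzyme elevation, plus tests on which the criteria set no limit.

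**3. How many could be missed.** The inputs are 400 per arm and 20% early discontinuation (both from section IV), giving 400 x 0.8 = 320 completers per arm. Two rates are assumed, because the protocol gives none: 4-8% newly abnormal at week 24, of whom 30-70% are back in range by week 48.
- Low end: 320 x 0.04 x 0.30 = 3.8.
- High end: 320 x 0.08 x 0.70 = 17.9.

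That is about 4 to 18 per arm. Completers are the right base, because for a patient who leaves between weeks 24 and 48 the week-24 result may be the last one and so be counted.

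**4. How much a difference is diluted (illustration; every rate is assumed).** Take 400 per arm. Let b be the share abnormal at baseline (5-25%), of whom 80% are still abnormal at week 48. Among the rest, i is the share newly abnormal at week 24 (10% in one arm, 5% in the other), r the share of these resolved by week 48 (25-75%), and 2% of those still normal become abnormal at week 48.
- Any new abnormality among patients normal at baseline: i + 0.02(1 - i). This gives 0.118 and 0.069, a difference of 4.9 points.
- Last-visit proportion: 0.8b + (1 - b)[i(1 - r) + 0.02(1 - i)]. The difference between arms reduces to (1 - b) x 0.05 x (0.98 - r).
- b = 0.05, r = 0.25: 0.95 x 0.05 x 0.73 = 3.5 points.
- b = 0.25, r = 0.75: 0.75 x 0.05 x 0.23 = 0.9 points.

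The factor (1 - b) is the dilution from baseline abnormality, and (0.98 - r) is the loss from resolution. XII.7 names no test, but as a yardstick, the power of a comparison of two proportions would be 54-64% for new abnormalities and roughly 5-35% for the last-visit proportion. In the lower-rate arm, 43-89% of last-visit abnormalities would be pre-existing.

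**The case against.** There is a good case that this matters little.

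- **The rule says mainly, not only.** The second sentence of XII.7 promises an analysis of changes after treatment, which refers to the pre-treatment value. This stands in part. The sentence could cover week 24 and shifts from baseline, but it commits to neither, and a mean change can hide a few large individual rises.
- **Adverse event reporting.** X.2 tells investigators to watch laboratory tests for toxicity and to record events whether or not they are drug-related, X.6 follows events until they are normal or nearly so, and XII.6 compares the arms. An abnormality that prompted action would very likely appear there. This stands. What remains exposed is the out-of-range value that nobody records as an event.
- **Entry criteria and randomization.** The exclusions remove much baseline abnormality, and randomization balances the rest on average. This also stands: it limits the overcount and makes it noise, not bias.
- **Shared glibenclamide.** Five pills contain 5 x 0.25 = 1.25 mg, the same as half a 2.5 mg tablet, and both arms follow the same titration steps. Known glibenclamide risks are therefore largely common to both arms. This is fair, but it does not remove the question of what the herbal component adds.
- **A matter for the statistical analysis plan.** XII.1 promises a separate plan, which was not available for this review, and shift tables are usual content for it. But XII.7 does not leave the main measure open. It states one, whereas XII.8 expressly defers the hypoglycemia comparison to that plan.

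A reader might infer that week-24 laboratory data go unreported, or that the measure favours one arm. The documents support neither.

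**Conclusion.** The point holds as a limited weakness in one safety summary. As stated, the main measure omits resolved week-24 abnormalities in completers and mixes pre-existing with new ones. The consequence is chiefly dilution of any between-arm difference in that summary. It is not a failure of safety reporting as a whole, and it does not touch the primary endpoint or any efficacy conclusion.

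The size cannot be fixed from the documents. About 4 to 18 missed patients per arm rests on the assumed 4-8% and 30-70% rates among some 320 completers. The shrinkage from 4.9 to between 0.9 and 3.5 points rests on the further assumptions shown, and takes 400 per arm with no allowance for discontinuation. Both are illustrations, not forecasts. The change is still worth making, because the data are already collected and the better measure costs almost nothing.

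**What to change.** In XII.7, define the main laboratory measure from the worst post-baseline value, using week 24, week 48 and any early-termination or unscheduled test, relative to the week -4 value. Count two things by arm: new out-of-range values in patients who were in range at screening, and worsening in patients who were already out of range. The second count is needed because a measure restricted to patients normal at screening would drop someone who enters with a mildly raised enzyme and then rises sharply. Show both in a baseline-to-worst shift table by arm, and keep the last-visit proportion as a supplement.

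The cost is one sentence in XII.7 and one table, with no new tests or visits. If the statistical analysis plan already contains such a table, XII.7 need only be brought into line with it.

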**8. Onset of hypoglycemia**

According to treatment group and visit time, the incidence of hypoglycemia in each patient will be summarized. Comparison between treatment groups will be described in the statistical analysis plan.

**9. Sub-group analysis**

If considered as appropriate, it may analyze the characteristics of each sub-group of the population (such as age, sex or current situation of treatment with oral hypoglycemic agents).

**10. Diagnostic and ranking standard for type 2 diabetes belonging to the syndrome of deficiency of both qi and yin**

The TCM symptom items were designed according to <TCM clinical diagnostic terms>, <standard for diagnosis and therapeutic effect of TCM symptoms>, the fifth edition of <TCM internal medicine>, <TCM symptom differentiation and diagnosis>, and <TCM quantization diagnosis>, on the basis of other literature and TCM commonly seen symptoms and signs of diabetes.

## XIII. Ethics requirements

Before the start of the clinical trial, the trial protocol can be implemented after reviewed and approved by the Ethics Committee and signed with suggestions for approval. During the trial, any amendment to the trial protocol can be performed only when approved by the Ethics Committee, any serious adverse events occurred in the trial should be reported to the Ethics Committee. The investigators must explain the details on the clinical trial to subjects, including:

1. The subjects are voluntary to participate in the trial, and have the right to withdraw from the trial at any time at any stage of the trial while they may not be subjected to discrimination or retaliation, and their medical treatment and interests will not be affected;

2. It must let the subjects understand that data on participation in the trial and the personal data in the trial are confidential. When necessary, the drug administrative department, the Ethics Committee or the sponsor can access the information of subjects participating in the trial according to the provisions;

3. It should inform the subjects the trial objectives, trial duration and process, inspection and operations, anticipated benefits and risks of the subjects, and inform the subjects that they may be assigned to different groups;

4. Subjects must be given sufficient time to consider whether willing to participate in the trial. For the subjects unable to express consent, it should provide their legal representative with the above description and instructions. It should use the language and words that can be understood by the subjects or their legal representative during the process of informed consent. During the trial, subjects can access the relevant information at any time;

5. If damage associated with the trial occurred, the subjects may get treatment and appropriate compensation.

The investigators will get informed consent from the subjects after full and detailed explanation of the trial. The subjects or their legal representatives will sign and date informed consent, the investigators who implement the process of informed consent also need to sign and date the informed consent form. For incapacitated subjects, if the Ethics Committee agrees in principle and the investigators consider their participation in the trial is in line with their own interests, then these patients can also enter the trial after their legal guardians agree and sign and date. In case of emergency when it is unable to get informed consent from the patients and their legal representatives, if it lacks of treatment method that has been proved as effective, while the test drug is expected to save lives, restore health, or alleviate pain, they can be considered as subjects, but it need to clearly state the method to accept these subjects in the trial protocol and relevant documents, and get prior approval from the Ethics Committee. If it founds new important information involving in the investigational drug, it must amend the informed consent in written form, which needs to obtain the subjects’ consent once again after approved by the Ethics Committee.

## IVI. Anticipated study results

1. The indicators of glycemic control in Xiaoke Pills treatment group and the glibenclamide group are similar.

2. Study of personalized therapy on the basis of molecular typing.

2.1 To identify 9-10 single nucleotide (SNPs) sites and other biomarkers (including metabolomics markers) that is guiding and promising in personalized therapy of type 2 diabetes with Xiaoke Pills in clinical practice.

2.2 To found 5-7 single nucleotide (SNPs) sites and other biomarkers (including metabolomics markers) that is associated with the special effects of Xiaoke Pills.

2.3 The efficacy of drugs To found 1-2 new important signaling molecule pathway factor that may affect the drug efficacy.

2.4 To develop a clinical protocol that can guide personalized therapy with Xiaoke Pills, improve efficacy of Xiaoke Pills and reduce side effects.

## XV. Expected progress and completion date of the clinical trial

2007.4—2007.12：

Organization of research team;

Design and preparation of detailed research protocol, Investigator’s Brochure, CRF

Implementation of research protocol and preparation of materials

Researcher training;
2008.1—2008.6

Kick-off meeting, investigator training;

Completion of enrollment and randomization

Treatment and follow-up

2009.6—2009.10

End of the trial, data analysis

**Appendix:**

**1. Diagnosis of overweight and obesity**

Chinese Diabetes Society of Chinese Medical Association suggests currently using BMI 24 and 28 recommended by China Working Group on Obesity as the diagnosis division point of overweight and obesity (Table 1). With the accumulation more precise epidemiological research data and deepening of people’s understanding of the disease, the division point will still change. For diagnosis of children and adolescents overweight/obesity, generally speaking, age-specific BMI 85 percentile or above and BMI 95 percentile or above in the BMI age-specific distribution curve of the background population are respectively defined as overweight or obese.

Table 1 Estimation of overweight/obesity in adults using body mass index

|  | BMI（kg/m2） |  | Risks of causing concomitant diseases |
| --- | --- | --- | --- |
| Classification | WHO(1998) | WHO-WPR(2000) |
| Low weight | <18.5 | <18.5 | low, but it will be increased when there are other clinical conditions |
| Normal | 18.5~24.9 | 18.5~22.9 | Common |
| Overweight | ≥25 | ≥23 |  |
| Pre-obese | 25~29.9 | 23~24.9 | increased |
| Obesity stage I | 30~34.9 | 25~29.9 | moderate |
| Obesity stage II | 35~39.9 |  | severe |
| Obesity stageIII | ≥40 |  | very severe |

Table 2 Diagnosis division point of overweight and obesity recommended by China Working Group on Obesity

| Weight | BMI（kg/m2） |
| --- | --- |
| Low weight | <18.5 |
| Normal | 18.5～23.9 |
| Overweight | 24.0～27.9 |
| Obesity | ≥28.0 |

Note: For comparability with international data, the data of BMI ≥ 25 kg/m2 and ≥ 30 kg/m2 should be calculated and included during statistics of the BMI data

2. Estimation of abdominal or central obesity (increased waist fat) using waist circumference or waist-hip ratio (WHR)

In recent years, abdominal obesity is usually diagnosed by waist circumference, but the division point used varies greatly among populations. The difference in WHR division point between populations is relatively small. Chinese Diabetes Society of Chinese Medical Association suggest currently using the waist circumference of 85 cm in males and 80 cm in females as the diagnosis division point of central obesity as recommended by China Working Group on Obesity (Table 3).

Table 3 Relationship between BMI and waist circumference with relative risk of obesity-related diseases of China *

| BMI（kg/m2） | Waist circumference（cm） |
| --- | --- |
| Males≤85 >85  Females≥80 >80 |
| <18.5  18.5～23.9 increase  24.0～27.9 Increase High  ≥28.0 high very high | |

* Relative risk refers to the risk of type 2 diabetes, hypertension and cardiovascular disease as compared with those with normal BMI and waist circumference,

**Xiaoke Pills Package Insert**

**Drug name**

Common name: Xiaoke Pills

Pinyin: Xiaoke Wan

**INGREDIENTS:**

Radix Puerariae, Radix Rehmanniae, Radix Astragali, Radix Trichosanthis, Stylus Zeae Maydis, Fructus Schisandrae Sphenantherae, Rhizoma Dioscoreae and Glibenclamide.

DESCRIPTION:

Black coated concentrated pills; sweet, sour and slightly astringent in taste.

**ACTIONS AND INDICATIONS:**

Nourish kidney-*yin*, replenish *qi*, promote generation of fluid. Indicated for diabetes due to deficiency of *qi* and *yin* (type 2 diabetes) manifested as polydipsia, polyphagia and polyuria, emaciation , fatigue, shortness of breath, indolent about speaking.

SPECIFICATION:

Per 10 pills weight 2.5g (contains glibenclamide 2.5mg).

